
#### Health economics measures

11)Child reported quality of life (CHU-9D) is a paediatric generic preference-based measure of health-related quality of life with nine dimensions (worried, sad, pain, tired, annoyed, school work/homework, sleep, daily routine and ability to join in activities), each with five response categories, which are scored 1–5 [33, 34]. The self-reported version of the measure, validated for use with children aged between 7 and 17 years old [34], will be administered to students at baseline and at 12-month follow-up.12)The Client Service Receipt Inventory (CSRI) is a bespoke service use questionnaire that will be used in this study to collect information on the frequency of additional school-based service use by students (e.g., Additional Learning Needs team) and parent-school consultations regarding bullying. Consenting parents will be asked to complete this retrospective CSRI questionnaire at 12-month follow-up. The CSRI will ask for above information for the preceding 6 months and will include associated questions regarding loss of earnings due to bullying-related consultations. CSRIs are widely used in health economics approach to gather information on participant service use. A repository of CSRI questionnaires is available (https://dirum.org/) to assist those developing CSRIs for economic evaluations.

##### Patient and Public Participation (PPI)

This study will use feedback from students, teachers and school leaders to review and improve key aspects of the research, including the trial design and the nature of written communication materials and initial training sessions. The reporting of patient and public involvement in this study will follow the short form Guidance for Reporting Involvement of Patients and the Public (GRIPP2-SF) [35].

#### Process evaluation measures

The MRC guidance on process evaluation will be used as a framework [36]. A mixed methods approach will be adopted. Quantitative methods will assess intervention fidelity, and recruitment of schools, students and parents/carers. Qualitative methods will examine implementation processes, operation of intervention mechanisms, the role of contextual factors and will interrogate patterns in the quantitative data. The quantitative data from the main trial (e.g., on hypothesized mediators) will explore operation of intervention mechanisms.

Implementation fidelity will be defined as the delivery of the main KiVa components (classroom lessons, universal actions at school level, indicated actions to deal with bullying incidents) in line with a minimum level of adherence. KiVa lesson implementation fidelity will be assessed by using data supplied by KiVa coordinators in each school which captures the number of KiVa lessons which each class has delivered. Adherence will be defined as delivery of at least 70% of lessons (of those due to have occurred at the time of reporting) in all classes within a school which are delivering KiVa as part of the trial.

Fidelity of classroom lesson implementation will be explored in further detail in a sample of 16 schools, in which researchers will observe and rate lessons using checklists produced by the KiVa intervention developers. These will assess the extent to which planned KiVa lesson activities are completed, and student learning and engagement. Researcher observation sheets will also include additional questions on the class environment and any challenges encountered during the lesson.

To assess fidelity of universal school level actions, permission will be sought to access existing fidelity checklists completed by KiVa trainers in each intervention school. These cover: a) provision of information on KiVa to staff, students and parents/carers; and b) promotion of the KiVa intervention across the wider school, including use of posters and staff tabards. To assess fidelity of indicated actions, each school will be asked to complete a termly checklist which captures the extent to which bullying incidents have been dealt with in line with the KiVa strategies, procedures and documentation. In each school where observation takes place, two lessons will be observed and where possible researchers will observe two teachers delivering the programme in each of the 16 schools.

**Factors affecting implementation**

In-depth case studies will be conducted in up to eight intervention schools (two per study site) to explore implementation processes, and how these vary across different school contexts. In each school, interviews will be conducted with: the KiVa Coordinator; a member of the KiVa team (which responds to bullying incidents); 1–2 class teachers involved in lesson delivery; and, if applicable other staff involved in intervention delivery. Interviews will explore staff experiences of, and key factors affecting implementation, its perceived value for their professional roles and schools, facilitators of, and barriers to, its integration within school systems and whether adoption of KiVa has led to changes in, or discontinuation of, other activities/policies. Staff will be asked about their receipt of intervention training and support, their confidence in dealing with bullying and the extent to which they perceive their school as having a strategy for bullying following KiVa adoption.

**Intervention mechanisms**

Up to three focus groups will be conducted in each case study school, with students (Years 4–6) who have received KiVa lessons, to examine acceptability, knowledge of KiVa content, and whether it has shaped peer interactions. In case study schools, we will also conduct interviews with approximately five parents/carers to explore the extent to which information about KiVa has been communicated to families, and its receipt by them.

Case study interviews and focus groups will enable us to refine understanding of key intervention mechanisms, and how contextual factors shape their operation. Qualitative findings on mechanisms – and their variation across schools, together with mediation analyses, will help to refine the intervention logic model. Data from case study schools will seek to identify any unintended (positive or iatrogenic) mechanisms.

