#### Secondary outcomes

i.Student-self-report outcomes:The OBVQ global item: “How often have you bullied others at school in the last few months?” will measure bullying perpetration. Students respond using the same five-point scale reported above that will be analysed continuously and dichotomised, with scores of 2 to 4 classified as perpetration and scores of 0 to 1 as no perpetration.Subjective student wellbeing in school will be measured using the “How I feel about my school” (HIFAMs) [27]. The survey is comprised of seven items which ask students how they feel about various aspects of school life, for example how they feel when completing their school work or when they are in the playground. This survey will be administered at baseline and at 12-month follow-up.Student empathy will be measured using the Empathy Toward Victim Scale [28]. The seven-item measure asks respondents to rate their level of empathy towards victims on a Likert scale anchored from ‘never’ (0) to always (3).Roles in bullying situations will be measured using the “Participant Role Questionnaire” (PRQ) [28], designed to identify the different roles that peers play in bullying situations. The questionnaire identifies the five different bullying roles; bully, assistant, reinforcer, defender and outsider. The respondent rates how often they behave in the ways described for each role on a three-point scale (Never, Sometimes, Often).ii.Teacher-report student outcomes: these will be measured through teacher survey reports for each child:5.Teacher-reported Strengths and Difficulties Questionnaire (TSDQ) [29] will be administered at baseline and follow-up to measure student mental health. These 25-item screening instruments are widely used in developmental, social, clinical and educational studies to detect behavioural, hyperactive/inattentive, emotional, and peer problems and pro-social strengths in children. The standard version asks about behaviours observed over the previous 6 months. The TSDQ is brief, quick to complete, and validated in national UK samples.iii.Student-level data collected from schools:6)School administration staff will provide student-level records of authorised and unauthorised half-day school absences for eligible students for the year prior to baseline and during the intervention year. These data are routinely collected by schools for all students as a legal requirement. Schools will ensure that student anonymity is protected.7)At follow-up, data from the Absence and Exclusion, and KS2 attainment datasets will be requested from the National Student Database (NPD) for students in both trial arms.iv.Individual staff-level outcomes. We will measure the following secondary outcomes through survey self-reports from teaching staff from KS2:8)Adapted version of the 5-item Challenging Behaviour Self-Efficacy Scale, designed as a measure of teacher self-efficacy related to challenging behaviours and adapted to specifically refer to bullying behaviours [30].9)Warwick-Edinburgh Mental Wellbeing Scale [31]. This 14-item positively worded scale measures adult mental wellbeing with good test-retest reliability (*r* = 0.83) and high internal consistency (a = 0.89). This measure will be administered at baseline and at 12-month follow-up.10)Maslach Burnout Inventory-General Survey (MBI-GS) [32], an introspective 22 item psychological Inventory. It provides a three-dimensional description of emotional exhaustion, depersonalisation, and personal accomplishment.

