### Data collection

Table 1 summarises the timetable for data collection. Baseline data was collected in April–July 2021 via student and teacher surveys (teacher-reported measures in March–May and child reported (year 3, 4 and 5 students) measures in April–July 21). The same measures will be collected approximately 12 months post-baseline (May–July 2022) for students in Years 4, 5, and 6. Absence will be collected in September 2021 and September 2022 for prior academic year.

**Table 1 Tab1:** The Stand Together Participant Timeline (SPIRIT figure): schedule of enrolment, interventions and assessments

Measure	Enrolment	Baseline	Allocation	End of academic year data	Intervention period	Follow-up 12 month post-randomisation
	Dec 20-April 21	April–July 21	May 21	Sept 20/21 Sept 21/22	Sept 21-July 22	May 22–July 22

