**PUPIL –REPORTED ASSESSMENTS:**						
How I Feel About My School (HIFAMS)		X				X
Child Health Utility 9D (CHU9D)		X				X
Olweus Bullying and Victimisation Questionnaire (OBVQ)		X				X
Participant Role Questionnaire (PRQ)		X				X
Empathy for the Victim Scale (EFTVS)		X				X

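### Candidate mediators and victimisation share the only survey wave after randomisation, so the planned mediation analyses cannot tell mediation from reverse dependence

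*Protocol article*

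**What the plan says.** Examining intervention mechanisms is a stated aim (Abstract, Methods and Discussion). Under Process evaluation measures the article says: "The quantitative data from the main trial (e.g., on hypothesized mediators) will explore operation of intervention mechanisms". Under Intervention mechanisms it says that the qualitative findings, "together with mediation analyses, will help to refine the intervention logic model". It does not name the mediators or the method. The Intervention section gives the theory: changed bystander behaviour takes away the social reward for bullying.

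On timing, Data collection says: "The same measures will be collected approximately 12 months post-baseline (May–July 2022) for students in Years 4, 5, and 6". Table 1 places the role questionnaire (PRQ), the empathy scale, the modified teacher self-efficacy scale and the Olweus questionnaire (OBVQ) in the same two columns, baseline and follow-up. The primary-outcome item asks about being bullied over the preceding couple of months.

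On the role measure, Secondary outcomes says: "The respondent rates how often they behave in the ways described for each role on a three-point scale", with the answers never, sometimes and often.

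**The concern.** A mediation claim needs the mediator to change before the outcome. Here the only mediator value after randomisation comes from the same survey wave as the outcome, and the outcome item refers to a period before that visit. An analysis plan can choose a better model, but it cannot add a missing wave.

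The role questionnaire adds a second difficulty. Assisting, reinforcing or defending requires bullying to be happening, so a frequency rating may move with the amount of bullying. KiVa has routes other than bystanders: the Intervention section describes scripted indicated actions for confirmed cases, and high-visibility vests that make break-time supervision more visible. If one of these lowers bullying, role scores could fall as a result.

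What is at stake is the mechanism conclusion. The logic model could be revised on an association that runs from outcome to mediator.

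**Working it through.** **1. Timing, from Table 1, Data collection and Process evaluation measures**

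| Measure | Baseline | During KiVa year | Follow-up | Both arms |
|---|---|---|---|---|
| Victimisation (OBVQ) | yes | no | yes | yes |
| Participant roles (PRQ) | yes | no | yes | yes |
| Empathy | yes | no | yes | yes |
| Teacher self-efficacy | yes | no | yes | yes |
| Lesson counts, termly indicated-action checklists | no | yes | no | no, KiVa delivery only |

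The only quantitative measures scheduled during the year describe KiVa delivery. They have no control-arm counterpart, so they cannot serve as mediators compared across arms.

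**2. The plan's own figures, used only to anchor the simulation**

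- Individual-level size: (1.960 + 1.2816)² × (0.18×0.82 + 0.14×0.86) / 0.04² = 10.507 × 0.268 / 0.0016 ≈ 1,760 per arm, or 3,520 in total, as stated.
- Design effect: 1 + (111 − 1) × 0.02 = 3.2.
- Schools: 3,520 × 3.2 / 0.9 / 111 = 112.8, rounded up to 114 (an even number), plus 2 lost schools = 116, as stated.

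**3. Can a role score that is not a mediator look like one?**

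Set-up: 58 schools per arm and 100 students per school (111 × 0.9 = 99.9). Victimisation is 18% against 14%, with ICC 0.02 through varying school rates. Bystander propensity is standard normal and not changed by arm. The reported role score is

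latent score = propensity + d × log(school bullying rate / 0.16), cut into three levels.

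Here d is the assumed dependence on the amount of bullying; the documents give no figure for it. Path a is the arm effect on the role score, and path b is the role-score effect on victimisation given arm. Both use school-clustered standard errors. A false result means that both paths have |z| > 1.96. The spurious share is mean(a × b) / mean(total effect). There were 400 runs per setting. The drop from 18% to 14% shifts the latent score by about d × log(0.14/0.18) = −0.251 × d.

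| d | Latent shift (SD) | False result, 18% v 14% | Mean a × b | Share of total (about −0.040) | False result, 18% v 18% |
|---|---|---|---|---|---|
| 0 | 0 | 0.5% | 0.0000 | 0.0% | 0.0% |
| 0.25 | −0.06 | 15.5% | −0.0002 | 0.6% | 1.75% |
| 0.5 | −0.13 | 55.25% | −0.0009 | 2.3% | 2.0% |
| 1.0 | −0.25 | 92.5% | −0.0032 | 7.9% | 5.5% |

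The Monte Carlo standard error is about 2.5 points at 55% (√(0.55×0.45/400)) and 1.1 points at 5.5% (√(0.055×0.945/400)). The models had no baseline adjustment; its effect on these rates was not examined.

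**4. Defending**

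Suppose KiVa truly raises defending propensity by 0.15 SD. The arm effect on the latent reported score is then about 0.15 − 0.251 × d: +0.09 at d = 0.25, +0.02 at 0.5 and −0.10 at 1.0. It crosses zero near d = 0.6. In simulation (200 runs per setting) the mean indirect effect was +0.0003, +0.0001 and −0.0014 at these values. So a real gain can be hidden or reversed.

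**The case against.** **The plan's claim is modest.** It speaks of exploring mechanisms and helping to refine a logic model, alongside case studies and triangulation. That stands, and it lowers the severity. Case studies in up to eight intervention schools still cannot settle direction in the quantitative data.

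**Much rests on material not shown.** Mediators, mediation method and PRQ scoring are not given, and an analysis plan is promised. It stands that the PRQ's dependence on the amount of bullying is inferred from its response format, and that its place as a mediator is inferred from the bystander theory. For empathy and teacher self-efficacy only the timing point applies. The timing point does not depend on an analysis plan, because the article itself fixes the schedule.

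**Baseline values exist.** They allow adjustment for starting level but do not supply order.

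**A sub-study is mentioned.** Amendments to ethical approval refers to one on changes in bullying behaviour over time. The article gives no schedule or sample for it and no link to the mediation analyses, so it cannot be counted. A mid-year measure in both arms would weaken the timing point where it was taken.

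**Arm contrasts are already planned.** Roles, empathy and self-efficacy are secondary outcomes compared by arm. That is right; what is new is baseline adjustment, their priority as mechanism evidence, and labelling.

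**A stronger reading.** A reader might infer that the analyses will report mediation where there is none. The documents do not support this. It needs both a KiVa effect by another route and a role score that tracks bullying. Without the second the false rate was 0.5%; without the first it was at most 5.5%. Nor is a large spurious share supported when scores follow bullying in the school. For defending, the artefact works against the theory.

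**Conclusion.** The point holds as a limit on what can be concluded. Every candidate mediator comparable across arms has one value after randomisation, taken in the outcome's own wave, so mediation and reverse dependence cannot be separated. This part follows from the schedule and needs no assumption.

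The risk of a false mechanism is conditional. If KiVa lowers victimisation from 18% to 14% by a non-bystander route, and role scores track school bullying with d between 0.25 and 1.0, a two-path test passes falsely in about 16% to 93% of trials. The spurious share is about 0.6% to 8%, so the harm is a falsely significant mechanism rather than a large mediated proportion. The range of d and the school-level form of the dependence are assumptions. Severity is low: the comparison of victimisation between arms does not use these analyses.

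**What to change.** 1. Make the randomised arm contrast on each candidate mediator, adjusted for its baseline value, the lead quantitative evidence on mechanism. Statistical methods lists only the stratification variables, age and sex as covariates, so the baseline value has to be added.
2. Report mediated effects as cross-sectional associations, with a sensitivity analysis for the reverse direction, for example the same model with victimisation as the intermediate variable and the role score as the outcome.
3. Do not revise the logic model on the mediated effects alone.
4. Interpret arm contrasts on raw PRQ scores with the caveat that they may reflect less bullying rather than changed bystander propensity. Randomisation does not remove this.

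Re-scoring each role as a share of the child's total role score may look attractive but is not advised. If never is scored zero, the share is undefined for a child who answers never throughout, and the share for defending rises mechanically whenever bully, assistant or reinforcer scores fall.

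The cost is analysis-plan wording and a few extra models on data already scheduled. The downside is a weaker quantitative claim about mechanism.

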**Usual practice**

All schools will be asked at recruitment and follow-up to complete a pro-forma (via an interview with a researcher) describing their policies and practices in relation to preventing and dealing with bullying incidents. These data will enable a description of UP that will inform future research. In each study site the key school link member from three control schools will be invited to take part in an interview to further explore UP in relation to bullying.

#### Routinely collected data

At follow-up, participants’ parents will be provided with information and an opportunity to opt their child out from their child’s trial data to be linked with their routine education data. Children’s identifiers: Name, School, Year Group, DoB (where available), Gender (where available) will be provided by sites to enable this linkage. Education data will be requested from the NPD in England and student attainment dataset in Wales via their formal approval processes. Data requested will be related to some demographic information (Ethnicity, special educational needs), attendance, and academic attainment from the Key Stage 2 assessment to enable a comparison between trial arms. Data from the trial will be sent to the ONS Secure Research Service, a secure data safe haven used by the Department for Education and linked on a record level with the data from the NPD using the participant ID.

### Data collection

Table 1 summarises the timetable for data collection. Baseline data was collected in April–July 2021 via student and teacher surveys (teacher-reported measures in March–May and child reported (year 3, 4 and 5 students) measures in April–July 21). The same measures will be collected approximately 12 months post-baseline (May–July 2022) for students in Years 4, 5, and 6. Absence will be collected in September 2021 and September 2022 for prior academic year.

**Table 1 Tab1:** The Stand Together Participant Timeline (SPIRIT figure): schedule of enrolment, interventions and assessments

Measure	Enrolment	Baseline	Allocation	End of academic year data	Intervention period	Follow-up 12 month post-randomisation
	Dec 20-April 21	April–July 21	May 21	Sept 20/21 Sept 21/22	Sept 21-July 22	May 22–July 22
**ENROLMENT:**						
Headteacher informed consent	X					
Informed of allocation			X			
**INTERVENTIONS:**						
*KiVa intervention-intervention arm only*					X	
*Usual practice-control arm only*					X	
*Usual practice data*	X					X
**PUPIL –REPORTED ASSESSMENTS:**						
How I Feel About My School (HIFAMS)		X				X
Child Health Utility 9D (CHU9D)		X				X
Olweus Bullying and Victimisation Questionnaire (OBVQ)		X				X
Participant Role Questionnaire (PRQ)		X				X
Empathy for the Victim Scale (EFTVS)		X				X
**TEACHER QUESTIONNAIRE:**						
The Strengths and Difficulties Questionnaire (TSDQ)		X				X
Maslach Burnout Inventory Manual		X				X
Modified Self Efficacy Scale		X				X
The Warwick – Edinburgh Mental Well-being Scale (WEMWBS)		X				X
School attendance, exclusions and academic attainment				X		
Process evaluation-teacher interviews/ focus groups					X	
Process evaluation-teacher interviews/ focus groups					X	
Routine data						X
Child Health Utility-9D (CHU-9D)						X
Client Service Receipt Inventory (CSRI)						X

### Data management and security

Student and teacher names were collected and stored securely on password protected folders at respective research sites, separate from any trial data. Student-reported and teacher-reported trial data are being entered on to an offline Qualtrics application system on tablet screens in the first instance, with a paper version of each questionnaire (to be subsequently entered onto the Qualtrics database) as a back-up in case of any technical issues or school request. Pseudonymised trial data will be uploaded to Qualtrics and exported to Excel or SPSS for data checks and cleaning prior to data analysis. All paper CRFs will be stored at sites, prior to being transferred by courier to the CTR. Paper CRFs will be stored securely in locked cupboards and all electronic data will be stored securely on password-protected secure Cardiff University servers. Data transfer to site researchers for additional analysis will be via the Cardiff University secure Fastfile system.

Qualitative interview and observation recordings will be recorded on encrypted audio-recorders/video recorders and stored on password-protected computers at sites. Recordings will be securely transferred to the study team at the CTR by Fastfile or courier. All files will be encrypted, and transcripts will be fully pseudonymised prior to analysis. All qualitative interviews will be audio-recorded, transcribed fully, and pseudonymised for analysis. Computer software (NVivo) will be used to manage the qualitative data and transcripts.

Data security and confidentiality will be ensured, in line with GDPR. A data management plan will be completed and adhered to. Only the trial team will have access to the final study dataset.

